### Sample Size Calculation

The sample size is calculated using G^*^Power 3.1.9.4 (University of Kiel) for the expected results of physical performance (6MWT) and mental well-being (depression). While 6MWT is a standardized measurement to assess physical capacity in patients with chronic disease during rehabilitation, e.g., COPD, (87–89) it was used as the primary outcome of physical performance for sample size calculation. 6MWT was also conducted in the first inpatient rehabilitation studies with patients with COVID-19 and showed good feasibility (31, 55). Multiple regression analyses assess the baseline situation of patients after acute COVID-19 with regard to physical resilience or mental health at the beginning of the inpatient rehabilitation. Due to the novelty of the disease, there are no representative comparative values for associations between COVID-19 and physical resilience and mental health. Therefore, the calculation of sample size in the cross-sectional analysis refers to the generic effect size measure *f*^2^. According to Cohen (97), a mean effect size of *f*^2^ = 0.15 will be used to calculate the sample size. Results from studies on correlations in patients with pneumological diseases (e.g., COPD) are used to justify this selected effect size in more detail. The study by Zeng et al. (98) identified age, severity of disease, and quality of life as significant predictors for physical performance measured by 6-minute-walking-distance in patients with COPD with a medium effect size of *f*^2^ = 0.21. In a regression model, von Leupoldt et al. (99) showed that depression is one out of 6 predictors (e.g., age, gender, forced expiratory volume in 1 s) for the completed 6MWT in COPD-patients in outpatient rehabilitation with a small effect size of *f*^2^ = 0.06 (71). Due to the heterogeneity of study results, a medium effect size of *f*^2^ = 0.15 can be assumed for the calculation of sample size to present associations between physical performance and mental health. With a planned power of 80% and significance level of 5%, 92 data sets are required, considering up to 5 potential predictors (e.g., pulmonary function values, blood gas values, age).

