To detect the outcomes over time, differences between 2 dependent samples (T1 and T2) will be analyzed. The minimal clinically important difference between two measurement time points is 30 meters for the 6-minute-walking-distance (88). According to experience from our own studies on physical performance in patients with occupational respiratory diseases, standard deviations between 80 and 100 m are to be expected (100, 101). Assuming a standard deviation of 100 m (due to heterogeneity of the sample) and an expected effect size of d = 0.3, 71 data sets are required with a power of 80% and significance level of 5%.

While a drop-out rate of 25% is expected during the study period of 21 months, a total sample size of at least 115 patients will be included.

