### Statistical Analysis

IBM SPSS Statistics Version 28 and AMOS Version 28 (IBM Corp., Armork, NY, USA) will be used for all statistical analyses.

First, to determine the existing outcomes of COVID-19 on physical capacity, psychological and cognitive well-being, and the ability to work at the beginning of inpatient rehabilitation (T1), the population will be descriptively characterized by all measured outcomes. Data from participants at the end of inpatient rehabilitation (T2) and at the follow-up time points (T3, T4) will be analyzed to further evaluate the long-term outcomes of patients with COVID-19 undergoing an intensive rehabilitation in terms of physical capacity, psychological and cognitive well-being, and the ability to work. Normal distribution and homoscedasticity of the sample will be realized using the paired *T*-test or Wilcoxon-test. Depending on the feasibility for the current population, group differences (e.g., age, gender, pre-existing conditions, comorbidities, current employment) in the long-term effects of COVID-19 on physical capacity, psychological and cognitive well-being, and the ability to work will be analyzed separately for the different time points (T1, T2, T3, T4) using different statistical methods as follows. Taking into account the number and size of groups, normal distribution and homoscedasticity of the sample, parametric or non-parametric statistical methods such as the *T*-test, Mann-Whitney *U*-test, ANOVA, or the Kruskal Wallis test will be used. To evaluate the associations between the different outcome measures of physical capacity, psychological and cognitive well-being, and ability to work, correlation analysis will be performed to measure the strength of the relationship between two variables, e.g., 6MGT and HADS-D or 6MGT and WAI. Depending on these results and current insights from the literature, multivariate and logistic regression analyses accounting for confounders such as age, gender, or comorbidities will be conducted to identify predictors or meditators of the long-term outcomes of COVID-19. For example, a logistic regression analysis will be used to examine the relationship between physical capacity, psychological and cognitive well-being and the dependent variable return to work 6 or 12 months after the start of inpatient rehabilitation. For all analyses, Bonferroni correction for multiple testing will be applied and statistical significance level will be set to *p* < 0.05. After inspecting the amount and pattern of missing data and outlier values, the most appropriate procedure for addressing both factors will be selected.

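### Single-step Bonferroni is fixed for all analyses; Holm's step-down gives the same 5% family-wise control, never has less power, and gains 0 to about 11 points per test depending on how many effects are real

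*Protocol article*

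**What the plan says.** The Statistical Analysis section of the protocol article names one multiplicity method and allows no exception: "For all analyses, Bonferroni correction for multiple testing will be applied". The same sentence adds that the "statistical significance level will be set to *p* < 0.05". It mentions no stepwise procedure and does not say which tests form a family.

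Three outcomes are each called primary for their own area: the MoCA under Neurocognitive Measurements, the 6MWT under Physical Performance Measurements and the WAI under Measurements to Assess Work Ability. Statistical Analysis also covers data at T2, T3 and T4, subgroup comparisons, correlations and regressions.

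The Sample Size Calculation section works at 5% without adjustment. For the regression: "With a planned power of 80% and significance level of 5%, 92 data sets are required, considering up to 5 potential predictors". For the paired T1 to T2 comparison of the 6MWT it takes d = 0.3 and arrives at 71 data sets. The recruitment target follows: "While a drop-out rate of 25% is expected during the study period of 21 months", and "a total sample size of at least 115 patients will be included".

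**The concern.** Single-step Bonferroni compares every p-value in a family of m tests with 0.05/m. Holm's procedure orders the p-values and compares the smallest with 0.05/m, the next with 0.05/(m − 1), and so on up to 0.05, stopping at the first that fails. It uses the same p-values, needs no assumption about their correlation and keeps the family-wise error at 5%. Every threshold is at least as large as Bonferroni's, so no data set exists in which it declares fewer results significant.

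For test decisions, plain Bonferroni therefore buys no extra protection. With three primary outcomes, several visits and only about 86 patients left after the expected drop-out, some real changes in walking distance, cognition or work ability could be reported as non-significant when an equally strict procedure would have declared them.

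**Working it through.** **Inputs from the article**
- Bonferroni for all analyses, overall level 0.05 (Statistical Analysis).
- 30 m difference and SD 100 m for the 6MWT, so d = 30/100 = 0.3 (Sample Size Calculation).
- 115 recruited, 25% drop-out: 115 × 0.75 = 86.25, taken as n = 86.

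**Assumptions, because the article gives no value**
- Family size m: 3 (the three named primaries) or 9 (three primaries × T2, T3, T4).
- Number k of real effects: varied from 1 to m.
- d = 0.3 for every real effect. The article supports this only for the 6MWT between T1 and T2.
- Correlation between test statistics: 0, 0.3 and 0.6.
- Two-sided paired t tests.

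**The plan's own figures first.** Regression with f² = 0.15, 5 predictors and N = 92 (noncentral F, noncentrality 0.15 × 92): power 80.4%, as planned. Paired test with d = 0.3: n = 71 gives 80.5% one-sided; two-sided, 80% needs n = 90 (80.4%). The article states no power after any multiplicity correction.

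**Bonferroni power at n = 86.** Noncentral t, 85 df, noncentrality 0.3 × √86 = 2.78:
- unadjusted 0.05: 78.5%
- m = 3, level 0.05/3 = 0.0167: 63.3%
- m = 9, level 0.05/9 = 0.0056: 47.9%

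**Holm against Bonferroni.** Simulation with 100,000 data sets per setting; average power per real effect, ranges over the three correlations:

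| m | real effects k | Bonferroni | Holm | gain (points) |
|---|---|---|---|---|
| 3 | 3 | 63% | 71–73% | 8 to 10 |
| 3 | 2 | 63% | 67% | 3 to 4 |
| 3 | 1 | 63% | 63% | about 0 |
| 9 | 9 | 48% | 59% | about 11 |
| 9 | 5 | 48% | 52% | about 4 |
| 9 | 3 | 48% | 50% | about 2 |
| 9 | 1 | 48% | 48% | about 0 |

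The number of real effects drives the result; the correlation matters much less.

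**Chance of at least one true finding.** Both procedures make their first rejection under the same condition, that the smallest p-value is at most 0.05/m. They differ here only if a false rejection comes first, and in every setting the two agreed to within 0.3 points.

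**Against the planned 80%.** At n = 90, two-sided, with all effects real: for m = 3, Bonferroni gives 65.8% and Holm 72.5 to 75.3%; for m = 4, Bonferroni gives 61.7% and Holm 69.9 to 72.8% (correlations 0 to 0.8). Holm recovers part of the loss, not all of it.

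**The case against.** The strongest reply is that nothing here is wrong. Bonferroni is valid, it is pre-specified, and it contradicts nothing else in the article. That stands: this is a matter of efficiency, not an error.

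A reader might infer that the plan gives away 8 to 11 points of power in every test, for nothing. The article does not support that, for four reasons.
- Those figures need every effect in the family to be real. With one real effect the gain vanishes.
- The families of 3 and 9 are assumptions. Each primary outcome is primary only within its own area, and the article nowhere pools them.
- It gives no effect size for the MoCA or WAI, or for T3 or T4. The 25% drop-out refers to the whole 21 months, so 86 pairs may be too few for T2.
- Bonferroni does offer something in return: simple simultaneous confidence intervals. The article mentions none, so the plan as described does not use this advantage, but it is not nothing.

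Nor does Holm have more power in every sense, since the chance of at least one true finding is practically the same.

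It can also be said that Holm cannot be applied until families are defined. That is true, but it applies equally to Bonferroni. The undefined family and the sample size set at an unadjusted 5% are separate and weightier matters, which this change does not solve.

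None of this removes the core of the point. At equal family-wise control, Holm's test decisions are never worse. The introduction expects rehabilitation to help in physical, neurocognitive and psychological domains, so several real effects in one family is a plausible case here, and that is where Holm gains most.

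**Conclusion.** The point holds as a cheap improvement to a valid choice. For test decisions, Holm's step-down is never less powerful than the single-step Bonferroni that the plan fixes, and often more powerful, at the same 5% family-wise level under any dependence.

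The size is conditional: up to about 11 points of per-test power if all effects in the family are real, a few points if only some are, and practically none if one is. These figures rest on d = 0.3 for every outcome, 86 pairs, two-sided tests and correlations up to 0.6. That Holm is never worse rests on none of these assumptions.

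**What to change.** In Statistical Analysis, replace the Bonferroni correction by the Bonferroni-Holm step-down procedure within each family to which the correction is applied, keeping the family-wise level at 5%. The families need to be named for either method to be usable.

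The cost is one phrase. No additional patients, data or software are needed: the ordered p-values from the SPSS output are compared with 0.05/m, 0.05/(m − 1), and so on. The drawback is that simultaneous confidence intervals matching the Holm decisions are less simple than Bonferroni intervals. The change should be made before outcome data are examined, because a later switch would look data-driven. It should not be presented as restoring the planned 80% power.

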
## Conclusion

Using the planned study protocol, long-term effects of OAC on physical capacity, mental health, and work ability will be assessed and described in detail. With a follow-up period of 12 months after the start of inpatient rehabilitation, the project makes an important contribution to the state of knowledge about the long-term effects of the disease. In addition, this study will present associations between physical capacity, mental health, and work ability, as well as the influence of age, gender, comorbidities, and occupation. Moreover, measures, occurring peculiarities, and the feasibility of the inpatient treatment procedure for patients with OAC will be documented. During and at the end of the project period, (interim) results and findings will be summarized in information brochures and presented at information events for the accident insurance institutions. When interpreting the results, it should be considered that the target group is a selective sample of patients with the diagnosis of COVID-19 as a recognized occupational disease or work-related accident. In Germany, the BG Hospital for Occupational Disease Bad Reichenhall is a clinic specialized in the treatment and rehabilitation of occupational diseases and consequently appropriate for the investigation of this sample group. A randomized, controlled study design cannot be applied in the context of the current research project. Since the progression of COVID-19 is acute and associated with direct health-related consequences, it is ethically and medically irresponsible to deny affected insured persons inpatient rehabilitation over a longer period. Nonetheless, the results of the current study will contribute to further developing recommendations for monitoring and coordinating targeted and tailored inpatient rehabilitation in the context of sustainable rehabilitation management for patients after COVID-19. This can help optimize the procedures and processes of post-COVID rehabilitation with the aim to improve the patients‘ physical and mental health, and to support individual occupational ability. Finally, the results will provide a basis for further research, such as the development of disease-specific, health-promoting, and rehabilitative strategies for the sustainable healthcare of patients with COVID-19.

## Ethics Statement

The studies involving human participants were reviewed and approved by the Ethics Committee of the Chemnitz University of Technology (TU Chemnitz), Faculty of Behavioural and Social Sciences (number V-427-17-KM-COVID-19-18022021) and by the Ethics Committee of the Bavarian State Medical Association (number 21092). The patients/participants provided their written informed consent to participate in this study.

## Abbreviations

6MWT: 6-Minute Walk Test
BG: “Berufsgenossenschaft”
= German Social Accident Insurance Institution
COPD: Chronic Obstructive Pulmonary Disease
COVID-19: coronavirus disease 19
cpm: counts per minute
DGUV: “Deutsche gesetzliche Unfallversicherung”
= German Social Accident Insurance
ICU: intensive care unit
MoCA: Montreal Cognitive Assessment
OAC: Occupationally Acquired COVID-19
PTSD: posttraumatic stress disorder
RKI: Robert Koch Institute
SARS-CoV-2: severe acute respiratory syndrome coronavirus type 2
T1/T2/T3/T4: measurement time point 1/2/3/4
TU Chemnitz: Chemnitz University of Technology
WHO: World Health Organization.
